| Measurements and procedures: | 
Eligible, consenting adults will be prepared for general anaesthesia in the usual way consisting of EKG, pulse-oximetry, Narcotrend™, a venous cannula and an arterial line for continuous blood pressure monitoring. They will receive additional non-invasive monitoring for this study, such as transcutaneous measurement of pCO2 and O2, NIRS, and thoracic electrical impedance tomography (EIT, PulmoVista® 500, Draeger, Luebeck, Germany)
 
Standard pre-oxygenation (until etO2 is > 90% or time > 3 minutes) will be done. Anaesthesia will be started (= "induction") using Propofol and Fentanyl i.v., using Narcotrend™ to measure depth of anaesthesia. All patients will receive a standard dose (Rocuronium, 0.9mg/kg) of neuromuscular blockage to facilitate airway management and total intravenous anaesthesia will be installed to maintain anaesthesia. Train of four measurement (TOF) will be confirmed full neuromuscular blockage with Rocuronium every 30 seconds. If necessary, additional dosage of neuromuscular blockage will be administered.
 
After administration of Rocuronium, possibility of mask ventilation will be confirmed and the sealed envelope with the randomization will then be opened. As a study intervention, the assigned method (HFNCT 70 l/min with either jaw thrust or laryngoscopy, or 10 l/min or 2l/min) will be installed and mask ventilation discontinued starting the apnoea period. Nasopharyngoscopy (EF-N slim, Acutronic, Hirzel, Switzerland) will confirm upper airway patency. Blood gas analysis will be conducted: baseline awake, start of apnoea, first minute after apnoea start, every 2 minutes thereafter with a maximum of 75ml in total. Other measurements (ECG, pulse-oximetry, blood pressure, NIRS, thoracic EIT, Narcotrend™, PtcO2, PtcCO2) will be measured continuously over the study period.
 
The study intervention will end when one of the following criteria (study end-points) is met: SpO2 <92%, PtcCO2 > 80 mmHg, pH < 7.10, potassium > 6.0 mmol/l, or time > 15 minutes.
 
When any of the end points is reached, patient-centred standard anaesthesia care will be continued, as planned for the case.
 
A post-operative interview will be conducted on the first post-operative day to evaluate injuries during airway management (e.g. bleeding, sore throat, hoarseness, lip injuries), pain, postoperative nausea and vomiting.
 |

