### **3.7 Justification of choice of study population**

The study participants are of all ages and genders. We want a heterogenic population presenting to the operating theatre each day. We exclude patients who are too sick to safely undergo our experiment or who could bias our physiological findings with their underlying disease.

For more see 7.1: eligibility criteria.

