Overall, we will include 100 patients, 25 per group. Patients will be blinded as to their group allocations. Double-blinding is not possible, as devices differ from each other.

This design allows us to focus our study on the primary outcome, since we ensure, that free air circulation (and possible CO2 clearance) is possible by visually assessing airway patency. Through measurement of extended vital parameters, we can identify physiologic influence of rising CO2 in anaesthetized patients undergoing apnoeic oxygenation.

In addition, demographic data will be extracted from the AIS. This only includes standard data, that is collected through routine normal clinical workflow, such as age, sex, weight, height, BMI, airway risk factors, underlying diseases, smoking habits, ASA physical health status and indication for the surgery.

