## 8.5 Assessments of outcomes

### 8.5.1 Assessment of primary outcome

Transcutaneous CO2 will be measured throughout the study period by TCM4, Radiometer™, Thalwil, Switzerland; by applying a probe over the patient's chest. This is a standard procedure used very often during anaesthesia without complications.

Increase in ptcCO2 in mmHg/min will be calculated by dividing the difference of ptcCO2 by the time of the measurement, once linear increase has set in. In our pilot study, we have found transcutaneous ptcCO2 to have a little delay (about 60-90 seconds) after which linear rise sets in.

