### 10.2 Determination of Sample Size

We assumed that with maximal flow of 70L O2/min and maximal mouth opening, there would be the least increase of  $p_{tc}CO_2$ /min. Patel et al. showed an increase of only 1.13mmHg using this technique [2]. However, this was  $etCO_2$  instead of  $p_{tc}CO_2$ . According to Gustafson et al., who measured  $p_{tc}CO_2$  as well as  $p_aCO_2$ , the  $CO_2$  increase was in fact 1.8mmHg/min, with a standard deviation of 0.35mmHg [3]. This correlated very well with our own findings in our pilot study (not published).

Using a non-inferiority design, a difference of means of 0.3mmHg/min, a standard deviation of 0.35mmHg/min, an alpha of 0.025 (one-sided) and a power of 80%, the necessary sample

size calculates to 22 patients per group. Therefore, we will include 25 patients in each group to account for possible drop outs. A value of 0.3mmHg/min would still only result in a difference in increase of 9mmHg in 30 minutes of apnoea time. We defined this as measurable, but still clinically acceptable, because the normal range of standard arterial pCO2 is 11mmHg (35-46 mmHg) [6].

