### **10.3 Planned Analyses**

#### **10.3.1 Datasets to be analysed, analysis populations**

Distribution of data will be checked using qq-plots and swilk command in stata, normal distributed data will be presented as means and standard deviation, otherwise median and interquartile range will be used. Proportions will be presented as numbers and percentage. Analytical statistics uses Mann-Whitney u-tests and Students t-test, according distribution, or ANOVA and Kruskal-Wallis for multiple groups. Each of the groups will a-priori be compared to the control group independently, without correction of multiple comparisons. Other multiple comparisons or subgroup-analyses will be performed using correction factors. Proportions will be compared by Chi-square tests or Fisher's exact test. As sensitivity analyses, we will do regression analyses, using mixed effects linear regressions.

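### Making a covariate-adjusted model the primary analysis would use data already collected and could narrow the non-inferiority interval; the planned unadjusted test is valid but leaves that gain unused

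*Protocol*

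**What the plan says.** Section 10.3.1 sets the tests: "Analytical statistics uses Mann-Whitney u-tests and Students t-test, according distribution, or ANOVA and Kruskal-Wallis for multiple groups". Each intervention arm is compared separately with control. Mixed-effects regression is planned only as a sensitivity analysis, and no covariates are named.

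The primary outcome (8.5.1) is the difference in transcutaneous CO2 (ptcCO2) divided "by the time of the measurement, once linear increase has set in"; the section puts the delay before the linear rise at about 60 to 90 seconds.

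The candidate covariates are already collected:
- Section 6.1 extracts routine data "such as age, sex, weight, height, BMI, airway risk factors, underlying diseases, smoking habits, ASA physical health status".
- Section 6.1 installs the ptcCO2 sensor before pre-oxygenation, and the synopsis records the signal continuously. Under 6.2.1 the envelope is opened only after mask ventilation is confirmed, so a ptcCO2 value from before allocation is known should exist for each patient.
- Arterial gases are also taken: "Blood gas analysis will be conducted: baseline awake, start of apnoea, first minute after apnoea start, every 2 minutes thereafter".

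Randomisation is stratified by BMI in three bands and by smoking and age (synopsis, 6.2.1, 7.3). Section 3.7 says of the population: "We want a heterogenic population presenting to the operating theatre each day".

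**The concern.** The result depends on whether the upper confidence limit for a difference in mean slope stays below 0.3 mmHg/min, with 22 to 25 patients per arm. If pre-allocation ptcCO2, weight or sex predicts the slope, that between-patient variation widens the interval without telling us anything about flow rate. A chance imbalance in such a variable also moves the estimate in the one trial that is run. One control arm serves all three comparisons, so an atypical control arm would move all three together. A model using these variables needs no new measurement, yet the protocol ranks regression below the unadjusted test.

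The Mann-Whitney branch adds a second difficulty. Section 10.1 states the hypothesis as a difference of means against 0.3 mmHg/min, and a Mann-Whitney test gives no interval for that quantity.

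**Working it through.** **Inputs from section 10.2.** "Using a non-inferiority design, a difference of means of 0.3mmHg/min"; "a standard deviation of 0.35mmHg/min"; "an alpha of 0.025 (one-sided) and a power of 80" per cent; 22 per group needed and 25 enrolled. A true difference of zero is taken from the pilot finding in 10.1.

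**The plan's own figure.** n = 2 × [0.35 × (1.960 + 0.842) / 0.3]² = 21.4, rounded up to 22. This matches the protocol, with no covariates involved.

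**Unadjusted two-sample t-test.** SE = 0.35 × √(2/n).
- n = 22: SE = 0.1055, 42 df, power 79.3% by non-central t (81.1% by normal approximation).
- n = 25: SE = 0.0990, 48 df, power 84.4% (85.8%), 95% half-width 2.011 × 0.0990 = 0.199 mmHg/min.

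**Adjusted model, all four arms together.** R², the share of slope variance explained by the covariates, is an assumption. With k covariate terms and N patients:
- SE = 0.35 × √(1 − R²) × √(2/n) × √f
- f = 1 + k/(N − 4 − k − 1), the expected penalty for estimating the covariate effects
- residual df = N − 4 − k

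For k = 3 (ptcCO2, weight, sex): at N = 88, f = 1 + 3/80 = 1.0375 with 81 df; at N = 100, f = 1 + 3/92 = 1.0326 with 93 df.

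| Assumed R² | Power, 22 per arm | 95% half-width, 25 per arm |
|---|---|---|
| 0 | 79% | 0.200 |
| 0.1 | 83% | 0.190 |
| 0.2 | 87% | 0.179 |
| 0.3 | 91% | 0.167 |
| Unadjusted two-sample test | 79% | 0.199 |

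Example, R² = 0.2 and n = 22: SE = 0.3130 × 0.3015 × 1.0186 = 0.0961; 0.3/0.0961 = 3.12; power 87%.

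**Cost if the covariates explain nothing.** An unadjusted model pooling four arms has power 80.2% at 22 per arm and 85.1% at 25. Three useless covariates reduce this to 78.8% and 83.9%, a loss of about 1 to 1.5 points. Adding the strata as main effects takes five more terms (BMI 2; smoking and age 3), so k = 8. At N = 88, f = 1 + 8/75 = 1.107 with 76 df, and power is 76.1%, about 4 points lower.

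**Why pool the arms.** Fitting each pair of arms separately with three covariates gives f = 1 + 3/38 = 1.079 at 22 per arm. Power is then 76, 80, 85 and 89% for R² of 0, 0.1, 0.2 and 0.3, so much of the benefit goes.

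**Chance imbalance.** At 25 per arm the standardised difference in an unstratified covariate has SD √(2/25) = 0.283. It exceeds 0.5 SD in about 8% of pairwise comparisons. If that one covariate carries the whole R², a 0.5 SD imbalance moves the slope difference by √R² × 0.35 × 0.5 = 0.055, 0.078 or 0.096 mmHg/min for R² of 0.1, 0.2 or 0.3. That is 18, 26 or 32% of the margin.

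**The case against.** The strongest reply is that nothing is wrong. In a randomised trial the unadjusted test keeps its type I error, and its standard error already allows for chance imbalance. The SD of 0.35 is used without any covariate reduction, so the sample size already carries the between-patient variation. This stands. A reader might infer that the trial is underpowered or its estimate biased; the documents support neither.

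A reader might also infer that the endpoint ignores starting CO2. It does not: the slope subtracts a starting value. Because the linear phase begins after the delay, that value falls after allocation. What goes unused is the pre-allocation level as a covariate, and no section shows that this level predicts the slope.

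Body size is partly balanced already through BMI stratification, so imbalance in weight is less free than imbalance in sex or ptcCO2. This also stands.

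No section links the rate of rise to weight, sex or starting level, so the gain is assumed and may be nil. Nor is adjustment free beyond a few degrees of freedom: estimating the covariate effects also inflates the variance, as computed above.

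Finally, covariate lists commonly belong in a statistical analysis plan, and their absence here is not a finding. The ranking of the analyses is different, because section 10.3.1 itself settles it.

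**Conclusion.** The point holds as a possible gain in efficiency and in protection against chance imbalance, not as an error in the plan. The unadjusted test is valid and 22 per group is correct on the protocol's inputs.

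The size rests on an R² the documents do not give. With three covariates in one four-arm model, the change against the unadjusted two-sample test runs from nothing at R² = 0 to about 12 points of power at 22 per arm and 0.032 mmHg/min of half-width at 25 per arm (0.199 − 0.167) at R² = 0.3. Those figures take the residual SD as 0.35 × √(1 − R²) and exclude the strata terms, which take back part of the gain.

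A firmer benefit does not depend on R²: a linear model gives an interval for the difference of means that section 10.1 tests, which the Mann-Whitney branch does not. Overall this is an optional improvement of low to moderate severity.

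**What to change.** Amend section 10.3.1 so that the primary estimate is the adjusted difference in mean ptcCO2 slope, each arm against control, from one linear model fitted to all four arms. Include arm, ptcCO2 at envelope opening, weight, sex, and the BMI and smoking/age stratification factors as main effects. Compare the upper 97.5% confidence limit for each difference with 0.3 mmHg/min. Keep the unadjusted comparison as the sensitivity analysis. Do not adjust for values taken after the envelope is opened, since the team is unblinded from then on and the assigned method may already have affected them.

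The cost is a sentence or two of text and recording the time of envelope opening. No extra patients or measurements are needed. The statistical price, if the covariates turn out uninformative, is about 1 to 1.5 points of power with three covariates and about 4 points at 22 per arm with eight terms, relative to an unadjusted pooled model. The sponsor should accept that price knowingly when choosing the terms.

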| Outcome(s):   | 
Primary outcome: mean ptcCO2 increase in mmHg/min during apnoea time, measured transcutaneously.
 
Secondary outcomes: in case of desaturation within the predefined apnoea time: time (in seconds) until desaturation from SpO2 100% to 92%, measured by pulse oximetry. Changes in ptcO2, paO2 and paCO2 in mmHg/min, blood gas analysis parameters, upper airway patency, influence of jaw thrust vs. continuous laryngoscopy on CO2 clearance during HFNCT, changes in brain oxygenation (measured by near infrared spectroscopy (NIRS)) during apnoea time, changes in electrical impedance tomography (EIT) to validate ventilatory effect and pulse contour analysis to monitor cardiac output.
 |
| Study design: | 
Prospective, single centre, randomised controlled trial with four groups:
 

1) high flow 70 l/min of oxygen, using jaw thrust

2) high flow 70 l/min using continuous laryngoscopy

3) medium flow 10 l/min using jaw thrust

4) low flow 2 l/min using jaw thrust

                                                                                                                                                                                                                                                                                                                                                                                                                                                                                     |

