## 5.2 Secondary Outcomes

Secondary outcomes:

- Seconds until desaturation from SpO2 100% to 92% measured by pulse oximetry (if occurring at all)
- Lowest saturation
- ptcO2 rise in mmHg/min
- Airway patency (yes/no)
- Vital parameters (BP, HR, SpO2)
- Arterial pH, paCO2 and paO2
- Cerebral Oxygenation (NIRS)
- Highest etCO2 measured in the first minute after securing airway in mmHg
- TOF
- Cardiac output
- Changes in lung volume measured by EIT

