## 6. STUDY DESIGN

### 6.1 General study design and justification of design

Single blinded randomised controlled prospective trial (High-flow 70 l/min using two different techniques, medium-flow 10 l/min and low-flow 2 l/min, each with 100% oxygen).

Four interventions will be applied.

- High-flow nasal cannula oxygen **70** l/min using OptiFlow™ system by Fisher&Paykel™ and an oxygen inspiration concentration FiO2 of 100%, with continuous laryngoscopy
- High-flow nasal cannula oxygen **70** l/min using OptiFlow™ system by Fisher&Paykel™ and an oxygen inspiration concentration FiO2 of 100%, performing jaw thrust
- Medium-flow nasal cannula oxygen **10** l/min using Carbamed digiflow, Aquapak Hudson RCI to humidify oxygen and standard nasal cannula with 100% oxygen, performing jaw thrust
- Low-flow nasal low-flow oxygen **2** l/min using Carbamed digiflow, Aquapak Hudson RCI and standard nasal cannula with 100% oxygen, performing jaw thrust

The departmental digital Anaesthesia Information System (AIS) will be used to screen patients for compatibility.

Once written informed consent is obtained, after patients were given enough time to validate their participation and considering all possibilities, and pregnancy has been excluded in female patients (in all female patients: pregnancy test before inclusion), the patient will be brought to the operating theatre. After local anaesthesia, an arterial cannula will be placed

into the radial artery and arterial blood gases will be drawn. All necessary monitoring (EKG, pulse oximetry, EIT, NIRS, Narcotrend™, transcutaneous pCO2) will be installed and pre-oxygenation will begin. Once etO2 has reached 90% or more than three minutes have passed, induction of anaesthesia will begin using a TCI system for both Propofol and Remifentanyl. For neuromuscular blockage, Rocuronium 0.9mg/kg will be administered.

After induction of general anaesthesia confirmed by absent respiratory movement, unconsciousness, and according to Narcotrend™-values; mask ventilation will commence. If for whatever reason mask ventilation is still impossible after full relaxation and placement of a Guedel tube, the experiment will be discontinued immediately, and the airway will be secured by the anaesthetist.

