#### 8.5.3.2 Laboratory parameters

Arterial blood for blood gas analysis will be drawn awake, immediately after apnoea sets in, after one minute of apnoea and thereafter every two minutes. All in all, this makes ten blood gas analysis, for each of which we need to draw about 7.5 ml of blood. This is a study related measurement and not part of normal workflow.

Parameters analysed will include:

- pH
- $p_a\text{CO}_2$
- $p_a\text{O}_2$
- Saturation
- base excess
- bicarbonate
- potassium

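### Continuous secondary outcomes with a pre-allocation value are compared by tests that take no baseline covariate, which costs precision but causes no bias

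*Protocol*

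**What the plan says.** Protocol section 10.3.1 sets one family of tests for all continuous outcomes: "Analytical statistics uses Mann-Whitney u-tests and Students t-test, according distribution, or ANOVA and Kruskal-Wallis for multiple groups". None of these takes a covariate. Regression has a supporting role only: "As sensitivity analyses, we will do regression analyses, using mixed effects linear regressions". No covariates are named for it. Section 10.3.3 treats any departure from the planned analyses as a deviation to be listed and justified.

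Starting values are collected. Section 8.5.3.2 gives the gas schedule: "Arterial blood for blood gas analysis will be drawn awake, immediately after apnoea sets in", then at one minute and every two minutes. The synopsis agrees: "Blood gas analysis will be conducted: baseline awake, start of apnoea, first minute after apnoea start". In section 6.1 the arterial cannula is placed and the first gas taken before pre-oxygenation, and "All necessary monitoring (EKG, pulse oximetry, EIT, NIRS" and the other sensors are also attached before it starts.

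Section 5.2 lists several of these outcomes without saying whether a level or a change is meant: blood pressure, heart rate, SpO2, arterial pH, paCO2 and paO2, "Cerebral Oxygenation (NIRS" and cardiac output. The synopsis describes some of them as changes, for example "changes in brain oxygenation (measured by near infrared spectroscopy (NIRS)) during apnoea time", and gives paO2 and paCO2 as changes in mmHg/min.

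**The concern.** With 25 patients per arm, chance differences in starting physiology are to be expected. Randomisation is stratified on BMI, smoking and age, not on any starting gas or haemodynamic value. A comparison of later levels carries those chance differences into the estimate and widens its interval. A change score removes them only partly, and at low correlation it adds noise.

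The secondary hypotheses in section 10.1 are worded as absence of a significant difference or change. Where the expected result is that nothing is found, low precision makes that result easier to reach. The trial already collects the data that would narrow the intervals.

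**Working it through.** **The plan's own figure.** Section 10.2 uses a margin of 0.3 mmHg/min, an SD of 0.35 mmHg/min and "an alpha of 0.025 (one-sided) and a power of 80" per cent. With a true difference of zero:

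n = 2 × [0.35 × (1.960 + 0.842) / 0.3]² = 21.37, rounded up to 22 per group.

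This matches the stated 22, so the primary sample size is not in question.

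**Inputs for the secondary outcomes.** The 25 per arm comes from section 6.1. Three inputs are assumptions, because the documents set none of them for these outcomes: two-sided 0.05, a true difference of 0.7 SD, and a baseline-outcome correlation r of 0.5 to 0.7, with 0.3 and 0.9 shown as wider limits.

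**Variance of the arm difference, relative to comparing raw follow-up values (equal SDs at both times):**
- change score: 2(1 − r)
- linear model with baseline as covariate (ANCOVA): 1 − r²
- ANCOVA relative to change score: (1 − r²) / [2(1 − r)] = (1 + r)/2

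**Power.** Non-central t with 48 degrees of freedom. The non-centrality for raw values is 0.7 × √(25/2) = 2.475. It is divided by √[2(1 − r)] for change scores and by √(1 − r²) for ANCOVA. At r = 0.7, for example, ANCOVA has 2.475/√0.51 = 3.466 and change scores have 2.475/√0.60 = 3.195. Taking one degree of freedom for the covariate alters ANCOVA power by less than 0.1 point.

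| r | Change variance / raw | ANCOVA variance / raw | ANCOVA / change | Power raw | Power change | Power ANCOVA |
|---|---|---|---|---|---|---|
| 0.3 | 1.40 | 0.91 | 0.65 | 68% | 54% | 72% |
| 0.5 | 1.00 | 0.75 | 0.75 | 68% | 68% | 80% |
| 0.6 | 0.80 | 0.64 | 0.80 | 68% | 77% | 86% |
| 0.7 | 0.60 | 0.51 | 0.85 | 68% | 88% | 92% |
| 0.9 | 0.20 | 0.19 | 0.95 | 68% | about 100% | about 100% |

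**Other readings of the same result.** The difference detectable with 80% power from raw values is (1.960 + 0.842) × √(2/25) = 0.79 SD. With ANCOVA it is 0.79 × √0.75 = 0.69 SD at r = 0.5, and 0.57 SD at r = 0.7. Against raw values, adjustment is worth 25/0.75 = 33 patients per arm at r = 0.5 and 25/0.51 = 49 at r = 0.7.

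**If the baseline is uninformative.** In a simulation of 20,000 trials with 25 per arm, r = 0 and a difference of 0.79 SD, power was 78.9% unadjusted and 77.9% with ANCOVA, a cost of about one point.

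**Which baseline is safe.** In the synopsis and section 8.2.1, mask ventilation is confirmed and the envelope is opened; the assigned method is then applied. The synopsis starts the apnoea period at that step, and section 8.5.3.2 times the next gas just after apnoea begins. The awake gas, and any monitored value taken during mask ventilation before the envelope is opened, precede disclosure of the allocation. The start-of-apnoea gas does not.

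**The case against.** **The covariate that first comes to mind is post-allocation.** A reader might infer that the start-of-apnoea value is the natural baseline, particularly for paO2: pre-oxygenation may stop after three minutes whatever the etO2, so oxygen stores at that moment vary. But by then the allocation is known to unblinded staff and the assigned flow, jaw thrust or laryngoscopy is in place. Blood pressure, heart rate and cardiac output could already reflect the airway manoeuvre, and adjusting for such a value can remove or distort part of the effect. This objection stands and determines the fix.

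**Changes already use the starting value.** This also stands. The synopsis describes paO2, paCO2, NIRS and EIT as changes or rates. A reader might infer a gain of 24 points (68% to 92%) across the board. That figure holds only at r = 0.7 against raw values. Against change scores at r = 0.7 the gain is 4 to 5 points, at r = 0.9 it is nil, and for mmHg/min rates it may be negligible.

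**Model detail belongs in the SAP.** This stands in part. Covariates and time points are often settled there, and a plan not shown may do so. But section 10.3.1 is not silent: it names the main tests, and none can be adjusted. A later plan that adjusts them would change the stated analysis.

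**Unadjusted tests in a randomised trial are valid.** Agreed. A reader might infer bias or a threat to the primary result; the documents support neither. The section 10.1 hypothesis on vital parameters may also refer to change over apnoea rather than a difference between arms, which limits what rests on these comparisons.

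**Conclusion.** The point holds as one of efficiency in the secondary analysis. Section 10.3.1 fixes main comparisons that cannot use a baseline covariate, although pre-allocation values are collected. At an assumed correlation of 0.5 to 0.7, adjustment removes 25% to 49% of the variance of a raw-value comparison and 25% to 15% of that of a change-score comparison. The matching power gains are 12 to 24 points over raw values and 12 to 4 points over change scores, for an assumed 0.7 SD difference.

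The correlation and the effect size are assumptions; at r = 0.3 the gain over raw values is only about 4 points. Outcomes without a baseline, such as time to desaturation, airway patency and the highest etCO2 after the airway is secured, fall outside the point.

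**What to change.** In section 10.3.1, state that each continuous secondary outcome analysed as a level or change, and having a baseline, is compared between arms by a linear model with arm and that baseline as terms. Report adjusted differences from control with 95% CIs. Define the baseline as a value recorded before the randomisation envelope is opened:

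- blood pressure, heart rate, cardiac output and NIRS: the last monitored value during mask ventilation;
- pH, paCO2 and paO2: the awake gas.

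Use the start-of-apnoea gas as covariate only in a sensitivity analysis. Keep the rank tests for clearly non-normal outcomes, and the listed tests where no baseline exists. For a change measured from the same baseline value, the model gives the same arm effect whether the outcome is entered as level or change, so this also settles the difference between section 5.2 and the synopsis for those outcomes.

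The cost is mainly analysis wording, with no new patients or samples. The sponsor should confirm that cardiac output is recorded before the envelope is opened: the arterial line is in place, but section 6.1 mentions this measurement only during the intervention. If the correlation is near zero, about one point of power is lost. The awake gas precedes pre-oxygenation, so it may correlate only weakly with later paO2, and the gain there may be small.
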